### Sample size

To ensure that study has adequate power to determine the effectiveness of the intervention to improve outcomes of interest, we have powered our study on physical function after 12 months measured using the PROMIS-29. We believe that this will provide adequate power to examine differences in additional key outcomes (e.g., quality of life, anxiety, medication use, etc.) We calculated the sample size based on a two-sided, two-sample *t*-test at a significance level of 5%. The literature on minimally important differences in the PROMIS-29 domains suggests it is equal to 0.45–0.5 SD (4.5–5.0 points on a T-score metric). A 0.45–0.5 SD between group difference equates to a standardized effect size d between 0.45 and 0.5. As no similar cluster randomized controlled trial has been reported in the literature and Long COVID, ME/CFS, and other PIFI are heterogeneous, we have assumed that the intraclass correlation will be low (ICC = 0.1). Adjusting for this clustering of our primary outcome between 20 clinicians, we estimate that 600 patients (300 per condition, 30 per clinician cluster) will provide us with between 80.0% and 87% power. Assuming a loss to follow-up rate as high as 30% at the 12-month patient endpoint, we will aim to include approximately 856 patients (42 patients per clinician). In order to achieve balance in the proposed longitudinal cohort study, we will include 428 patients from the UW Medicine’s Post-COVID Telehealth Clinic.

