### Retention and withdrawal

In order to enhance retention in the study, all participating clinicians will be offered CME credit at no cost for their engagement in weekly teleECHO sessions and monthly interactive webinars. Clinicians will also be offered the flexibility to temporarily pause participation in sessions as an alternative to fully withdrawing. Participation in this study is voluntary. Participating clinicians may decide not to participate or may leave the study at any time. This decision will not result in any penalty or loss of benefits to which they are entitled. Information that has already been collected may still be used, but no new information will be collected. The withdrawal reason and the withdrawal date will be documented.

Clinicians who go on a leave of absence (LOA), while participating, will not be contacted about the study. Patients assigned to participating clinicians on LOA will remain a part of that clinician’s LC&FIRP patient assignment. However, if the patient seeks follow-up care, they will be scheduled to see another clinician participant in the same intervention arm. Additionally, clinicians who terminate their employment with FHCSD, retire, or move departments and are unable to see primary care patients will be withdrawn from the study. All of the data that they contributed up to the point of withdrawal will be included in the research. Patients assigned to clinicians who withdraw from the study will be reassigned to another participating clinician in the same intervention arm. Clinician participants who choose to temporarily pause participation will not be assigned new patients but will continue to see existing LC&FIRP patients within their panel.

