
### Statistical analysis

Analyses will be based on the intention-to-treat principle. All patients will be analyzed in the condition to which the clinician to which they were assigned was randomized regardless of compliance or fidelity. A “per-protocol” secondary analysis will be considered if compliance or fidelity of clinicians is a concern. All tests of significance will be two-sided and a *p*-value of 0.05 will be considered statistically significant. Group comparisons will be conducted on all the measured baseline patient characteristics to identify potential systematic differences between patients in each study arm. Identified patient characteristics that are not balanced will be used as covariates in the subsequent modeling of the data. Potential differential attrition between the two study arms will be compared and adjusted for in analyses. Analyses of differences in outcomes at both the patient- and clinician-level will include a linear mixed model to compare change in outcomes from baseline to each post-baseline assessment between the randomized study arms. Fixed effects will include the study condition, assessment, study condition-by-assessment interaction, baseline measure, and any unbalanced covariates. Assessment will be treated as a categorical variable, and an unstructured variance–covariance structure will be used. Results will be reported as point estimates (mean differences between groups) and interval estimates (95% confidence intervals). An intervention effect will be concluded if the *p*-value for the study arm-by-assessment interaction contrast in the model at the final assessment is statistically significant. This approach uses all available data and is robust to data missing at random (MAR).

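### The stated 80.0% to 87% power relies on a large-sample reference; the unadjusted comparison of 10 clinicians per arm has 18 degrees of freedom and about 75% to 83% power

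*Protocol article*

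**What the plan says.** The Sample size section of the protocol article powers the trial on PROMIS-29 physical function at 12 months, using a two-sided, two-sample t-test at 5%. It takes the minimally important difference as 0.45 to 0.5 SD ("4.5–5.0 points on a T-score metric"), which "equates to a standardized effect size d between 0.45 and 0.5". On clustering it says "we have assumed that the intraclass correlation will be low (ICC = 0.1"). After adjusting for 20 clinicians it concludes that "600 patients (300 per condition, 30 per clinician cluster) will provide us with between 80.0% and 87% power". Allowing for 30% loss to follow-up, it adds that "we will aim to include approximately 856 patients (42 patients per clinician").

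The section gives no degrees of freedom and mentions no small-sample correction for the number of clinicians. The Participants section puts 10 clinicians in each arm. The Statistical analysis section plans a linear mixed model with the baseline measure among its fixed effects and confirms that "All tests of significance will be two-sided".

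**The concern.** In a trial that randomizes clinicians, the precision of the between-arm comparison is estimated from the variation between clinicians. A design effect shrinks the effective number of patients, but it does not reflect that the variance is estimated from only 20 units. With so few units the critical value is noticeably larger than 1.96. A calculation that applies the design effect and then uses a normal or patient-level t distribution therefore overstates power.

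At stake is whether the trial reaches the conventional 80% at the lower end of its own minimally important difference. The section also relies on this calculation for adequate power on the other key outcomes. If the figure is too high, a null result would be read as stronger evidence of no effect than the design supports.

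**Working it through.** **Inputs, from Sample size and Participants.** Two-sided alpha 0.05; d = 0.45 and 0.50; ICC 0.1; k = 10 clinicians per arm; m = 30 completers per clinician, so 300 per arm; equal cluster sizes.

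**Step 1. Design effect and noncentrality.**
- Design effect = 1 + (m − 1) × ICC = 1 + 29 × 0.1 = 3.9.
- Effective patients per arm = 300 / 3.9 = 76.9.
- Noncentrality = d × √(76.9 / 2) = d × 6.20, which is 2.79 at d = 0.45 and 3.10 at d = 0.50.

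**Step 2. Reproduce the stated 80.0% and 87%.**

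| Reference distribution | d = 0.45 | d = 0.50 |
|---|---|---|
| Normal (critical value 1.96) | 79.7% | 87.3% |
| t, 598 df (600 patients − 2) | 79.6% | 87.2% |
| t, about 152 df (effective patients − 2) | 79.2% | 86.9% |

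All three lie within a point of the stated figures.

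**Step 3. Same noncentrality, cluster-level degrees of freedom.** df = 2 × 10 − 2 = 18 and the critical value is 2.10. Noncentral t power is **75.2%** at d = 0.45 and **83.4%** at d = 0.50. The gaps are 80.0 − 75.2 = 4.8 and 87 − 83.4 = 3.6 percentage points. A simulation of 200,000 trials of clinician means, each with variance 0.1 + 0.9/30, gives 75.3% and 83.4%.

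**Step 4. Is the difference usable power?** In the same simulation, testing clinician means against 1.96 gives 79.4% and 86.7%, but the type I error rises to about 6.5%. The extra points come from a test that exceeds its nominal 5%.

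**Step 5. Detectable difference.** On 18 df, 80% power needs a noncentrality of about 2.96, so d = 2.96 / 6.20 = 0.48. The normal reference gives (1.96 + 0.84) / 6.20 = 0.45.

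**Step 6. Would better retention close the gap?** With no loss at all, 856 / 20 = 42.8 completers per clinician gives 78.1% and 86.0% on 18 df. The shortfall comes mainly from the number of clinicians, not of patients.

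**Step 7. Baseline adjustment (illustrative).** The article gives no baseline correlation r. If r reduced the between- and within-clinician variance equally, d would be divided by √(1 − r²). On 18 df:

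| r (assumed) | d = 0.45 | d = 0.50 |
|---|---|---|
| 0.2 | 76.8% | 84.9% |
| 0.3 | 79.0% | 86.7% |
| 0.35 | 80.4% | 87.9% |
| 0.5 | 86.1% | 92.3% |

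**Step 8. Uneven cluster sizes (assumed).** Gamma-distributed sizes summing to 600 over 20 clinicians, clusters weighted by their information as a mixed model with a clinician random effect would do, 18 df. Mean power is 74.0% and 82.4% at a coefficient of variation (CV) of 0.4, and 73.2% and 81.7% at 0.5. That is 1 to 2 points below equal sizes.

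**Step 9. Enrolment figures.** 600 / 0.7 = 857 and 856 × 0.7 = 599, so 856 fits the target. But 42 × 20 = 840, and 840 × 0.7 = 588. At 588 completers (29.4 per clinician) power on 18 df is 75.0% and 83.3%, a change of about 0.2 points.

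**The case against.** The strongest reply is that the planned analysis is not an unadjusted t-test. The model includes the baseline measure, and Step 7 shows that a correlation near 0.35 would restore 80% at d = 0.45. This stands as a limit on the point: it cannot be said that the trial as it will be analysed has less than 80% power. It does not rescue the stated figure, which the article attributes to a two-sample t-test with no baseline correlation.

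The article also does not name its reference distribution, so the diagnosis is an inference. It is well supported: large-df references reproduce both figures closely, and 18 df misses both by more than rounding.

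The gap is modest. Power still exceeds 80% at d = 0.50, and the detectable difference of 0.48 SD stays inside the protocol's own 0.45 to 0.5 range.

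A reader might infer a much larger shortfall from uneven or lost clusters. Patients arrive by referral, clinicians who pause receive no new patients, and "Patients assigned to clinicians who withdraw from the study will be reassigned to another participating clinician in the same intervention arm". The documents do not support a large figure on either count:
- **Uneven clusters.** The usual inflation, 1 + ((1 + CV²)m − 1) × ICC, would give about 70% and 79% at a CV of 0.4. It weights every patient equally, whereas a mixed model with a clinician effect loses only 1 to 2 points. The CV is itself an assumption.
- **Lost clinicians.** No loss rate is given. The Statistical analysis section analyses patients by the arm of the clinician to whom they were assigned. If patients stay linked to that clinician in the model, a withdrawal removes no cluster.

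The 42 against 856 mismatch could also be read as under-enrolment. Both figures are called approximate in places, and the effect on power is negligible.

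**Conclusion.** The power statement is wrong as written. For the unadjusted two-sample comparison that the Sample size section names, with ICC 0.1, 10 clinicians per arm and 30 completers each, power on 18 df is about 75% at d = 0.45 and 83% at d = 0.50, against the stated 80.0% and 87%. The calculation reaches 80% at about 0.48 SD, not 0.45.

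This rests on the protocol's own inputs, equal cluster sizes and no baseline adjustment. Unequal sizes would lower power slightly further. Baseline adjustment would raise it by an amount that cannot be fixed from the article. The point corrects a published planning figure; it does not show that the design or the planned analysis is unsound.

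**What to change.** Replace the power sentence with: *With 20 clinicians (18 df), ICC 0.1 and 30 completers per clinician, power is about 75% for d = 0.45 and 83% for d = 0.50 before baseline adjustment.*

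If the baseline-adjusted mixed model is relied on to recover power, state the assumed baseline correlation and recompute on 18 df. As an illustration, r = 0.3 gives about 79% and 87% if it reduces both variance components equally. Add that uneven cluster sizes may cost a further 1 to 2 points, labelled as resting on an assumed CV of 0.4 to 0.5 and a clinician random effect.

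As a minor correction, make the enrolment figures agree wherever they appear: 856 patients is about 43 per clinician.

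The cost is a slightly less favourable power statement. No patients, clinicians or changes to the analysis are needed.

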## Discussion

This study will provide much needed high-quality evidence on the effectiveness of a technology-enabled multi-disciplinary team-based care model for the management of PCC, ME/CFS, and other PIFI within an FQHC setting, while simultaneously providing evidence regarding the feasibility, acceptability, and sustainability of the approach. Given that LC&FIRP includes a teleECHO program that is case-based, interactive, and occurs in real-time, it has a set of distinct advantages to the traditional practice of sequential in-person specialty referrals to address complex patient cases. This may be particularly helpful for cases in which the etiopathogenesis of PCC, ME/CFS, and other PIFI is unclear, as multiple specialist perspectives may be generated and discussed with the treating primary care clinician. It may also improve the targeted referral to local specialists to minimize unnecessary overuse of specialty care and reduce patient travel and time burden. We expect that the knowledge and confidence of participating clinicians will increase over time, that the cases presented to specialists will become more complex, and simpler routine cases will require consultation less frequently. This approach, which is clinician-focused, is nonetheless likely to result in more rapid provision of high-quality care for patients. We acknowledge that common clinical issues related to PCC, ME/CFS, or other PIFI will likely change over time. We consider our ability to measure this variation and explore its effect on a variety of clinician and patient outcomes as a strength. Taken together, findings from this research should inform how primary care providers and health system leaders support the clinical care of patients suffering from PCC, ME/CFS, and other PIFI.

## Trial status

This study was approved by Research Support Services at San Diego State University (Protocol Number: HS-2021–0241). This is protocol version 1.0 dated May 15, 2023. Recruitment began on November 30, 2021. The estimated study completion date is January 31, 2025.

## Data Availability

The datasets analyzed during the current study and statistical code will be available from the corresponding author on reasonable request, as is the full protocol.

## Abbreviations

CDC: Centers for Disease Control and Prevention
CME: Continuing medical education
CMIS: Clinical Management Information System
CNE: Continuing Nursing Education
CPE: Continuing Pharmacy Education
EHR: Electronic Health Record
FHCSD: Family Health Centers of San Diego
FQHC: Federally Qualified Health Centers
GAD: Generalized anxiety disorder
GEE: Generalized estimating equation
HAQ: Health Assessment Questionnaire
ICD-10: International Classification of Diseases Tenth Revision
IRB: Institutional Review Board
LC&FIRP: Long COVID and Fatiguing Illness Recovery Program
LOA: Leave of absences
MAR: Missing at random
ME/CFS: Myalgic encephalomyelitis/chronic fatigue syndrome
PCP: Primary care provider
PHQ: Patient Health Questionnaire
PIFI: Post-infectious fatiguing illnesses
PROMIS: Patient-Reported Outcomes Measurement Information System
PT: Physical therapy
PCC: Post COVID-19 conditions
REDCap: Research Electronic Data Capture
RT-PCR: Reverse transcription polymerase chain reaction
SME: Subject matter expert
SOP: Standard operating procedure
SNOMED CT: Systematized Nomenclature of Medicine—Clinical Terms
teleECHO: Extension for Community Healthcare Outcomes
UoC: University of Colorado
UNM: University of New Mexico
UW: University of Washington
